### Statistical analysis

Statistical analysis will be performed using the Statistical package for the Social Sciences (SPSS v. 24, IBM Corporation, Armonk, NY, USA). An *α* level will be established at 0.05 a priori for all statistical tests. Data will first be examined for normal distribution using the Kolmogorov-Smirnov test, and skewness and kurtosis parameters. Descriptive statistics will be performed to characterize the participants. Means, standard deviation, and frequencies will be obtained for both study groups. The chi-square test for frequency distributions will be used for demographics, and amputation type. Continuous data that are not normally distributed will be transformed prior to analysis.

The main analysis type that will be used to test the hypotheses of aims 1 and 2 will be a mixed-model, repeated measures approach. These analyses will examine the main effects of the exercise treatment on the study outcomes. The independent variables will include study group (HBRX or CON) and time point (baseline, week 12). Dependent variables will include LBP severity, medication use, perceived impact of LBP on QOL (NRS_pain_, medication number, SF-36, ODI, RMDQ) and biomechanical measures (walking velocity, temporal spatial parameters, GRF, key joint angles). Mixed models are the preferred approach to analyze data with repeated measures; these models account for correlation among repeated measurements, flexible time effects, and handle missing data. To test the hypothesis of aim 3, regression analyses will be used to identify significant contributors to the change in pain over 12 weeks. A hierarchical approach will be used to find the model of best fit. Independent variables that will be entered into the models will include changes in lumbar muscle strength, ultrasound measure of lumbar extensor cross-sectional area, and change scores in SF-36, ODI, and RMDQ. In addition to age, sex, and K-classification, models will be adjusted for other participant characteristics if differences are found from baseline to week 12 (Tampa Scale of Kinesiophobia and Pain Catastrophizing Scale scores, daily step number). Subjects who dropped out or missing participant data will not be included in the final analysis, and intention-to-treat will not be utilized. Due to the relatively small study size, actual treatment effects that would be seen may be washed out during an intention-to-treat analysis.

The study team, upon completion of the study, will make the results available in publication format, presented at relevant national scientific conferences and a summary of the results will be provided to each participant, electronically or by mail.

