### Study population

A total of 40 transtibial amputees aged between 18 and 65 years will be recruited for this study. Participants will be recruited from a major regional prosthetics center and from the greater north Florida community via relationships with local prosthetic clinics and amputee support groups. Study flyers, social media posts, and online web advertisements will also be used. Participants will be eligible if they meet the following inclusion and exclusion criteria. Inclusion criteria: men or women aged 18–60 years, traumatic transtibial amputation more than 1 year prior to enrollment, current prosthesis worn for at least 6 months, suffering from chronic LBP (>3 months with at least three pain episodes per week), must have regular access to a computer for Skype®, or a mobile phone or iPAD to perform Facetime; prosthesis K-level of K2 or greater (indicating the subject is able to ambulate and traverse low-level environmental barriers such as curbs, stairs, or uneven surfaces) [20]. Exclusion criteria: dysvascular amputation, acute back injury, pregnancy, any other chronic back pathology (i.e., herniated disc, ankylosing spondylosis, other related neurological disease), pain symptoms or functional limitations (including those that may require assistive devices) that preclude participation in resistance exercise or physical activity, back surgery within the past 2 years that restricts daily physical activities, and currently enrolled in any other resistance or strengthening exercise interventions. Written informed consent will be obtained from each participant.

The primary outcome of the study is the Numerical Pain Rating Scale (NRS_pain_) value for LBP. Sample size estimation indicated that a total sample size of 32 was necessary to detect clinically meaningful differences in NRS_pain_ from baseline to week 12. Based on published evidence of comparative studies of resistance exercise and controls on LBP [21], a sample size of 16 per group will yield a power of 80% at an *α* value of 0.05. To account for the anticipated dropout rate of 25%, the enrollment target will be 40.

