### Pain severity and pain impact on QOL

The primary outcome will be the change in the 11-point NRS_pain_ score during rest and activity from baseline to 3 months. The scale has anchors of 0 (no pain) to 10 (worst imaginable pain). The NRS_pain_ is an accepted outcome measure as described in the Initiative on Methods, Measurement, and Pain Assessment in Clinical Trials (IMMPACT) [38]. Participants will rate their current, worst, and best NRS_pain_ scores over the last 24 h, and the scores will be averaged to create the resting NRS_pain_ value [39]. The participants will also be asked to rate their pain severity during walking [40]. The number, type, scheduled nature of the medication and the medicine dose used to self-manage LBP symptoms will be self-reported by participants at baseline and weeks 4, 8, and 12.

One general QOL instrument and two disease-specific instruments will be used to determine the impact of LBP on participant perceptions of QOL [37]. General QOL will be measured by the Medical Outcomes Short Form-36 (SF-36), consisting of eight domain scores and two component scores (Mental, Physical). The SF-36 instrument has been used to track QOL after traumatic injury such as amputation [41]. Higher scores reflect higher QOL. Low back pain-specific QOL will be measured using the modified version of the Oswestry Disability Index (ODI) [42] and the Roland Morris Disability Questionnaire (RMDQ) [43]. The ODI contains 10 questions about the patient-perceived impact of pain on personal care, walking, lifting, sitting, standing, sleeping, sex life, social life, and traveling. The RMDQ consists of 24 items relating to difficulties with daily activities, house work, stair climb, walking, speed of movements, standing, appetite, and sleep. Both instruments are valid, reliable, reproducible, and sensitive to treatment interventions [42, 43]. Higher scores for both instruments reflect greater pain impact and disability due to pain.

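### The stated rule to transform non-normal data has no exemption for NRS pain, so the primary effect can leave the 0–10 point scale on which it is defined and sized

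*Protocol article*

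**What the plan says.** The Statistical analysis section of the protocol article sets a two-step rule. First, "Data will first be examined for normal distribution using the Kolmogorov-Smirnov test, and skewness and kurtosis parameters". Then, "Continuous data that are not normally distributed will be transformed prior to analysis". The check is described for the data; model residuals are not mentioned. The second step is not optional and exempts no outcome.

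The same section names the model: "The main analysis type that will be used to test the hypotheses of aims 1 and 2 will be a mixed-model, repeated measures approach". It lists NRS pain among the dependent variables, with study group and time point as the independent variables.

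The section Pain severity and pain impact on QOL defines the main endpoint as follows: "The primary outcome will be the change in the 11-point NRS_pain_ score during rest and activity from baseline to 3 months". It has two parts. For rest, current, worst and best ratings over 24 hours are taken and "the scores will be averaged to create the resting NRS_pain_ value". For activity, "The participants will also be asked to rate their pain severity during walking". The scale runs from 0 to 10.

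Under Study population, the total of 32 is described as "necessary to detect clinically meaningful differences in NRS_pain_ from baseline to week 12".

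**The concern.** The outcome definition and the sample size rationale both speak of NRS points. The transformation rule can take the primary analysis off that scale. A group-by-time effect on a log or square-root scale is not a difference in points, and it cannot be set against a clinically meaningful difference in points. It also gives the same fall in pain a different weight according to where the patient started.

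Whether this happens is decided by a test on the sample, so the effect measure of the primary analysis is not fixed in advance. Because the two parts of the primary outcome are built differently, one could be flagged and the other not, and the two results would then be on different scales.

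The check is also aimed at the wrong quantity. The normality assumption of the mixed model concerns its residuals, not the raw scores. Whole-number scores with many ties can fail a normality test even when the underlying variable is normal.

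**Working it through.** **The plan's own figure.** The protocol gives 16 per group, 80% power and α = 0.05, but no NRS difference and no SD, so the 16 cannot be reproduced. Solving backwards (two-sided, normal approximation): d = (1.960 + 0.842) × √(2/16) = 0.99; with the t-test, 1.02. If the SD of change were 2 points (assumed), this would be about 0.99 × 2 ≈ 2 points. The 2-point examples below are therefore of the right order. The point under review does not alter the sample size.

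**What a transformation does to equal falls.** The protocol names no transformation, so log(x+1) and the square root serve as examples.

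| Fall | Points | log(x+1) | Square root |
|---|---|---|---|
| 8 to 6 | 2 | ln(9/7) = 0.25 | 0.38 |
| 4 to 2 | 2 | ln(5/3) = 0.51 | 0.59 |
| 2 to 0 | 2 | ln(3/1) = 1.10 | 1.41 |

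**What it does to a contrast between arms.** Let one arm go from 6 to 4 and the other from 4 to 2.5, with every participant at the arm's value.
- Points: (4 − 6) − (2.5 − 4) = −0.5.
- log(x+1): ln(5/7) − ln(3.5/5) = −0.336 + 0.357 = +0.02.

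The sign reverses, although the log result is close to zero. The 2-point baseline gap is large for randomised arms: with SD 2 and 16 per arm its standard error is 2 × √(2/16) = 0.71, so the gap is 2.8 standard errors. This shows what can happen, not what is likely.

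**How often the check would flag NRS pain.** Scores were simulated from a normal variable, rounded and limited to 0–10, with n = 32 and 1,000 samples per setting. The means, SDs and the whole-number walking rating are assumptions. The table gives the percentage flagged at the 0.05 level.

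| Mean, SD | Whole number, Lilliefors-corrected | Average of three, Lilliefors-corrected | Whole number, uncorrected KS |
|---|---|---|---|
| 5, 1.5 | 80 | 13 | 6 |
| 5, 2 | 48 | 10 | 2 |
| 4, 2 | 48 | 10 | 2 |
| 3, 2 | 53 | 14 | 2 |
| 2, 2 | 79 | 29 | 5 |

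- A repeat with a similar set-up gave 51–57% for whole numbers and 7–15% for the average of three.
- At n = 16, as when arms are checked separately, the corrected test flags 21–42% of whole-number samples and 6–12% of averaged ones.
- If a flag also needs significant skewness or kurtosis, the whole-number rate at n = 32 falls to about 4–10% and the averaged rate to about 1–8%.
- In a further simulation the corrected test flagged one of the two pain scores but not the other in 50–63% of samples.

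**Error rates under the stated rule.** Assumptions: 16 per group, mean 5, SD 2, correlation 0.5 between visits, 2,000 runs, whole-number scores, and log(x+1) used whenever the corrected test flags either visit. The test was a t-test on change, which with complete data at two visits addresses the group-by-time effect. The SD of change before rounding is 2 × √(2 × (1 − 0.5)) = 2.

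| True effect | Rule triggered | Significant, always points | Significant, following the rule | Points and log disagree |
|---|---|---|---|---|
| 0 | 76% | 4.5% | 4.5% | 2.5% |
| 1 point | 74% | 27.3% | 27.4% | 9.4% |
| 2 points | 69% | 75.5% | 76.6% | 10.4% |

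Overall error rates barely move. The conclusion of an individual trial can still differ between scales.

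**The case against.** **The rule may rarely reach NRS pain.** The resting score is an average with fewer ties, and the protocol names skewness and kurtosis beside the Kolmogorov-Smirnov test. A rounded normal score has near-normal skewness and kurtosis, so a combined reading flags it seldom. This stands. A reader might infer that rounding alone will routinely push the primary outcome into transformation. The protocol does not support that: the high rates hold only for a whole-number score under a corrected test used alone, and the protocol does not say how its criteria combine.

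**Error control is not at risk.** A reader might infer a hidden extra test of the primary outcome, with inflated type I error or lost power. If an analyst could report the best of raw, log and square-root results, simulated type I error would rise from 4.5% to 5.8%. The protocol describes no such choice; it transforms when data are non-normal. Following that rule left type I error at 4.5% and power at 76.6% against 75.5%. This objection stands in full.

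**Details belong in the analysis plan.** The choice of transformation, the cut-offs and the residual checks are commonly left there, and their absence from an article is no fault. This also stands. The point rests only on the unconditional rule that the article does state.

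**An 11-point rating may not count as continuous data.** This is weak. The resting score is an average, NRS pain is entered in the mixed model as a dependent variable, and no other analysis is given for it.

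**Conclusion.** The point holds in a narrow form. Read literally, the protocol's transformation rule applies to NRS pain and can place the primary effect on a scale that cannot be read in points, in conflict with the outcome definition and the sample size rationale. The unequal weighting is plain arithmetic: for the same 2-point fall, the log(x+1) change is more than four times as large from 2 as from 8 (1.10/0.25 = 4.4). The reversed sign is an illustration with a large baseline gap.

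The chance of triggering cannot be fixed from the document. At 32 participants it ranges from about 1–3% to above 50% for a whole-number rating with assumed means of 3–5 and SD 2, depending on the test version and how the criteria combine. For the averaged resting score the corrected test gives 7–15% at those means, and 29% at an assumed mean of 2.

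The harm is to interpretability and to a fixed primary effect measure, not to type I error or power. It is modest, but it concerns the primary outcome and is nearly free to remove.

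**What to change.** Replace the rule, for the patient-reported scores, with a statement that NRS pain at rest and during walking is analysed in points on its original scale whatever the normality checks show. Apply the same to ODI, RMDQ and SF-36, because they are reported as scale scores; no calculation was made for these three.

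Assess model assumptions on the residuals of the mixed model. If they look poor, report a permutation or bootstrap p-value for the group effect, or an analysis on a transformation named in advance, as a sensitivity analysis only.

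The cost is one sentence and one extra analysis run. Sample size, visits and data collection do not change.

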### Randomisation and concealment

Following baseline measures, participants will be randomised to either the HBRX or the CON group. The randomisation will be performed by a clinical coordinator not involved in the study. Permuted block randomization [22] with block sizes of 4 will be made by means of a computer algorithm to ensure balanced group sizes and allocation concealment. Patients will receive an opaque, sealed envelope taken from a sequential order containing information on group allocation.

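### The only effect named for testing aims 1 and 2 is a main effect; read literally it estimates about half the treatment effect and does not match the change-from-baseline primary outcome

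*Protocol article*

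**What the plan says.** All references are to the protocol article.

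- **Statistical analysis**, model: "The main analysis type that will be used to test the hypotheses of aims 1 and 2 will be a mixed-model, repeated measures approach".
- **Statistical analysis**, factors: "The independent variables will include study group (HBRX or CON) and time point (baseline, week 12"). Baseline is thus a level of the modelled outcome, not a covariate.
- **Statistical analysis**, effect of interest: "These analyses will examine the main effects of the exercise treatment on the study outcomes". No interaction, change contrast or baseline-adjusted week-12 comparison is named for aims 1 and 2.
- **Pain severity and pain impact on QOL**: the primary outcome is the change in the NRS pain "score during rest and activity from baseline to 3 months".
- **Randomisation and concealment**: "Following baseline measures, participants will be randomised to either the HBRX or the CON group".
- **Study population**: "Sample size estimation indicated that a total sample size of 32 was necessary to detect clinically meaningful differences" in NRS pain between baseline and week 12, and "a sample size of 16 per group will yield a power of 80" per cent.

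**The concern.** With two visits and baseline among them, neither main effect is the treatment comparison that hypothesis 1 needs. The main effect of group is the HBRX-CON difference averaged over baseline and week 12. The main effect of time is the average change over both arms together, so it does not compare the arms. The difference between arms in change is the group-by-time term, and the text does not mention it.

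An analyst who follows the sentence as written would report an estimate of about half the true effect, from a test weaker than the one the sample size appears to assume. An analyst who reads it loosely would report group-by-time. Because the text does not settle which, the choice of primary test could be made after the data are seen.

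**Working it through.** **The plan's own figure.** The article gives 16 per group for 80% power at alpha 0.05, with no effect size, SD or sidedness. The figure can only be solved backwards. Two-sided, 16 per group corresponds to a standardised difference of 0.99 (normal approximation) or 1.02 (t test; 1.024 is used below).

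**Inputs.** From the article: n = 16 per arm, alpha 0.05, two visits, randomisation after baseline. Assumed: a two-sided test, equal SD σ at both visits, and correlation ρ between baseline and week 12 of 0.3, 0.5 or 0.7.

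**What each contrast estimates.** Let δ be the true HBRX-CON difference at week 12. The expected difference at baseline is 0.

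- Group main effect: expectation (0 + δ)/2 = δ/2; variance (2/n)·σ²·(1+ρ)/2.
- Group-by-time: expectation δ; variance (2/n)·2σ²·(1−ρ).
- Week-12 difference adjusted for baseline: expectation δ; variance (2/n)·σ²·(1−ρ²).

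Adding an interaction term to the model does not rescue the main effect while the main effect remains the test, because it still averages over both visits.

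**Relative strength.** The main-effect test statistic is sqrt((1−ρ)/(1+ρ)) times the group-by-time one: 0.73, 0.58 and 0.42 at ρ = 0.3, 0.5 and 0.7. Baseline adjustment has (1−ρ²)/(2(1−ρ)) = (1+ρ)/2 of the change-score variance: 65%, 75% and 85%.

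**Power, effect scaled to the change-score SD.** The group-by-time noncentrality is 1.024 × sqrt(16/2) = 2.90, which gives 80% on 30 degrees of freedom. Multiplying by the ratios above gives 2.12, 1.67 and 1.22 for the main effect. Dividing by sqrt((1+ρ)/2) gives 3.59, 3.34 and 3.14 for the adjusted test (29 degrees of freedom).

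| ρ | Group main effect | Group-by-time | Baseline-adjusted | n per arm for 80% on main effect |
|---|---|---|---|---|
| 0.3 | 54% | 80% | 93% | 29 |
| 0.5 | 37% | 80% | 90% | 46 |
| 0.7 | 22% | 80% | 86% | 86 |

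**Power, effect scaled to the raw SD** (δ = 1.024σ):

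| ρ | Group main effect | Group-by-time | Baseline-adjusted |
|---|---|---|---|
| 0.3 | 41% | 66% | 84% |
| 0.5 | 37% | 80% | 90% |
| 0.7 | 33% | 95% | 98% |

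At ρ = 0 the main effect and group-by-time have equal power, but the main-effect estimate is still halved. At every ρ above 0 the main effect is the weaker test.

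**Simulation check.** 40,000 trials with δ = −2, SD 2, ρ = 0.5 and 16 per arm gave a mean main-effect estimate of −1.00 with 35% power, and a mean group-by-time estimate of −2.00 with 78% power.

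**Chance baseline imbalance.** If the arms differ by D at baseline, the expected week-12 difference is δ + ρD. The main effect then has expectation δ/2 + D(1+ρ)/2, so it carries 0.65D to 0.85D over this range of ρ.

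**The case against.** The strongest reply is that the sentence is loose rather than wrong. It speaks of effects of the exercise treatment and does not say of group. The factor list is introduced as what the variables will include, which leaves room for an interaction. The primary outcome, the sample-size paragraph and the Discussion all speak of change from baseline to week 12, so the natural contrast is the between-group difference in change. A condensed article may also leave exact model terms to a fuller document. Much of this stands: the intended test may well be group-by-time. But the article does not leave the tested effect open. It names one, and that one does not correspond to its own primary outcome.

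A reader might infer three stronger things that the document does not support.

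- *That the trial is committed to testing a halved effect and will lose most of its power.* This depends on the literal reading and on an assumed correlation and scaling. At ρ = 0.3 on the change-score scaling, the fall is from 80% to 54%, about a third.
- *That a chance baseline difference passes in full into the result.* It enters the main effect at D(1+ρ)/2.
- *That leaving baseline out as a covariate is an error in itself.* Baseline is used, as an outcome level, and group-by-time is a valid test under randomisation. Adjustment is a gain in precision.

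**Conclusion.** The point holds as a badly fixed statement of the primary test. The only effect named for aims 1 and 2 is a main effect. Taken literally, the group main effect estimates about half the treatment effect and does not match the change-from-baseline primary outcome. The halving follows from randomisation after baseline and equal weighting of two visits; with unequal variances the weights would shift, but the estimate would still be diluted.

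The power figures are illustrations, because the article gives no effect size, SD or correlation. Over ρ from 0.3 to 0.7, main-effect power is 54% to 22% on the change-score scaling and 41% to 33% on the raw-SD scaling. Group-by-time has 80% on the first and 66% to 95% on the second. Whether the authors intended the literal reading cannot be settled from the document. The sentence governs the primary test, so it should be corrected before analysis.

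**What to change.** Replace the main-effects sentence with one that defines the treatment effect as the HBRX-CON difference at week 12 adjusted for the baseline value of the same outcome. Either ANCOVA, or a mixed model with a common baseline mean and the group-by-week-12 term as the treatment effect, will do. Report the estimate with its 95% confidence interval, and use the same contrast for NRS pain and for the other aim 1 and 2 outcomes.

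If the authors prefer not to adjust for baseline, naming the group-by-time contrast is the minimum valid correction.

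The cost is one sentence. No new data are needed, since baseline values are already collected and participants and visits are unchanged.

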## Methods

### Trial design

This study will be a single-assessor-blinded, pre-post-test randomised controlled trial. The study will follow the principles of the Consolidated Standards of Reporting Trials for randomized, two-group, parallel studies [18, 19]. Figure 1 provides the study flow and Fig. 2 shows a version of the Standard Protocol Items: Recommendations for Interventional Trials (SPIRIT) Figure for the trial. Details of study methodology are outlined in Additional file 1, SPIRIT Checklist. There will be an HBRX intervention group and a wait-list control group (CON). Outcome measurements will be performed before the intervention period (baseline assessment) and immediately after the 12-week intervention (post-testing assessment). Baseline and follow-up measurements will be evaluated blindly.

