### Wait-list control (CON) condition

Participants who are assigned to the CON group will wait to participate in the resistance training after a 12-week wait period. Participants will follow all instructions provided to them by their physician and care team, but will be asked to refrain from starting any new strengthening exercise protocols or begin any new physical therapies during this time. The participants will be contacted by phone on a monthly basis during the study period to determine if any changes in LBP symptoms, exercise schedule, or medication have occurred.

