### Primary outcome measures

Pain severity, QOL, and physical functioning are key components in a core outcome set for reporting of clinical studies for LBP [36, 37]. Outcome measures will be collected at our biomechanics laboratory during the subjects two baseline visits (week 0) as well as during the two post-intervention visits (weeks 12–13). Table 2 provides the summary of the study outcome measures.

**Table 2 Tab2:** Summary of outcome measures and participant characteristics. Collected weeks 0–1 (baseline) and 12–13 (post-intervention/wait-list controls)

Primary outcome measures	Data collection instrument or method
Back pain severity	11-point Numerical Pain Rating Scale (NRS_pain_)
	Resting and during activity
Pain impact on quality of life (QOL)	Pain medications used
	Medical Outcomes Short Form-36 (SF-36)
	Oswestry Disability Index (ODI)
	Roland Morris Disability Questionnaire (RMDQ)
Gait kinematics and kinetics	3D motion analysis for temporal spatial parameters of gait and trunk away, bilateral (at self-selected velocity, standard velocity)
	Ground reaction forces
Muscle strength	1-repetition maximum (1-RM) on MedX® clinical Machines: abdominal curl, hip adduction, hip abduction, leg press, and lumbar extension
Muscle morphology	Bilateral B-mode ultrasound measures of muscle thickness and cross-sectional area: multifidus, paraspinals, transversus abdominis, and internal oblique
Step count	StepWatch® monitor, 7-day average count
Participant characteristics	Demographics, weight, Body Mass Index, current medical issues, current medications
	Back pain history
	Pain catastrophizing level (Pain Catastrophizing Scale (PCS))
	Kinesiophobia (11-item Tampa Scale of Kinesiophobia (TSK-11))

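### With pain rated only at baseline and week 12 and dropouts excluded, the mixed model becomes a complete-case comparison of change for the primary outcome

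*Protocol article*

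**What the plan says.** The places that schedule the primary outcome agree.

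- **Trial design:** "Outcome measurements will be performed before the intervention period (baseline assessment) and immediately after the 12-week intervention (post-testing assessment".
- **Table 2 (Primary outcome measures):** "Collected weeks 0–1 (baseline) and 12–13 (post-intervention/wait-list controls".
- **Pain severity and pain impact on QOL (where the endpoint is defined):** "The primary outcome will be the change in the 11-point NRS_pain_ score during rest and activity from baseline to 3 months".
- **Statistical analysis:** "The independent variables will include study group (HBRX or CON) and time point (baseline, week 12".

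That last section then gives the reason for choosing a mixed model: "these models account for correlation among repeated measurements, flexible time effects, and handle missing data". It ends by excluding dropouts and participants with missing data from the final analysis and declining intention-to-treat. Compliance and attrition also excludes non-compliers.

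Contact between the two assessments already exists. Medication use "will be self-reported by participants at baseline and weeks 4, 8, and 12". Control participants are telephoned monthly "to determine if any changes in LBP symptoms, exercise schedule, or medication have occurred". HBRX participants are supervised weekly by video. No NRS rating is named at any of these contacts. The schedule in Fig. 2 is not reproduced in the text at hand, so this reading rests on the prose and Table 2.

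**The concern.** The stated reasons for the model do not fit the stated schedule and exclusions. With one post-baseline occasion there is no time course to model flexibly. Someone who leaves before week 12 supplies no pain score under treatment, and the exclusion rule then discards the baseline score too.

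What is at stake is bias more than power. Leaving an exercise programme because pain is not easing is plausible, and it has no counterpart on a waiting list. The HBRX participants who remain could then look better than the whole group. NRS pain during the 12 weeks, the variable most likely to explain such departures, is not recorded. Lifting the exclusion alone would not supply it.

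**Working it through.** **Inputs from the article:** 16 per group for 80% power at alpha 0.05; 25% dropout; 40 enrolled (Study population); blocks of 4, taken as 1:1.

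**Assumptions, not in the article:** two-sided test; NRS SD 2; correlation between ratings 0.5–0.7, either equal for all pairs or decaying with time (0.5–0.7 per four weeks); no true effect; a quarter of each arm lost, at random in CON.

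**1. The plan's own figure.** 32 × 1.25 = 40 reproduces the target. Dividing by the retained fraction gives 32/0.75 = 42.7, or 43. That is a separate matter. Here, 40 × 0.25 = 10 are lost and 30 remain, 15 per arm.

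**2. Power after exclusion.** No effect size is given. The implied one is (1.960 + 0.842) × √(2/16) = 0.99 SD. With 15 per arm, 0.99/√(2/15) − 1.960 = 0.75, giving 77.4% power.

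**3. What the model becomes.** When every analysed participant has both ratings, the group-by-time contrast equals the difference in mean change. No missing NRS value is left for the model to handle.

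**4. Possible bias.** Suppose the HBRX quarter with the highest score S leaves. The mean of S among completers falls by φ(0.674)/0.75 = 0.318/0.75 = 0.424 SD, or 0.85 points at SD 2. Other ratings fall in proportion to their correlation (ρ) with S.

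| S | Analysis of completers | Bias favouring HBRX (points) | Equal ρ, 0.5 / 0.7 | Decaying ρ, 0.5 / 0.7 |
|---|---|---|---|---|
| Week-8 pain | Baseline-adjusted | 0.85 × (ρ8,12 − ρ0,8 ρ0,12) | 0.21 / 0.18 | 0.40 / 0.45 |
| Week-8 pain | Unadjusted change | 0.85 × (ρ8,12 − ρ0,8) | 0 / 0 | 0.21 / 0.18 |
| Week-8 minus baseline pain | Unadjusted change | 0.85 × √((1 − ρ)/2), equal ρ | 0.42 / 0.33 | not tabulated |
| Week-4 pain | Unadjusted change | 0.85 × (ρ4,12 − ρ0,4) | 0 / 0 | −0.21 / −0.18 |

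The baseline-adjusted row is an approximation. Simulation with 20 per arm gave 0.18–0.22 (equal) and 0.38–0.47 (decaying), with the SD of the estimate about 0.5–0.75. With dropout only loosely tied to pain, the simulated bias was 0.07–0.22. The last row shows that bias can also run against HBRX.

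**5. With ratings at weeks 4 and 8.** When dropout depends on a rating already recorded, a likelihood analysis of all occasions brought the bias to near zero (at most 0.044 points in the settings run). When it depends on unrecorded pain at week 12 or at the missed visit, roughly a tenth to a half of the baseline-adjusted bias was removed. Measured against the unadjusted change contrast, it need not fall at all in that case.

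**6. Who gains, and power.** If departures spread evenly over 12 weeks, 10 × 2/3, or 6–7 of the 10, would have at least one post-baseline rating. At the effect in step 2, power is 77.4% excluding dropouts, 79.0–82.5% for a two-occasion model keeping baseline-only participants, and 80.3–82.7% with four occasions. For the same correlation, the four-occasion gain over two is 0.2–1.5 percentage points.

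**The case against.** **The exclusions are the main cause.** This is correct. While dropouts are discarded, their interim ratings would be discarded too. The two changes have to be made together.

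**The claim about missing data is not empty as a statement about mixed models.** A reader might infer that it is. A two-occasion likelihood model that kept baseline-only participants would use their baselines, assuming missingness depends only on observed data. The sentence also covers other outcomes, and medication is collected at weeks 4 and 8. What fails is narrower: as specified, with the exclusions, the advantages are not realised for NRS pain.

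**The benefit is partly built into the simulation.** A reader might infer that interim ratings eliminate the bias. That holds only when people leave because of pain already recorded.

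**Nor is it true that nothing collected could help.** Interim medication, control-arm symptom reports and exercise logs could inform imputation or sensitivity analyses. They are weaker than the rating itself, and the symptom calls and logs are specific to one arm.

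**The harm is modest, and the design is legitimate.** A bias of 0.2 points is about a third of the estimate's SD, and about a tenth of the implied effect if that is read on the same SD (0.99 × 2, about 2 points). Assessing at baseline and end of treatment is an accepted design. This limits the point to a cheap improvement.

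**Cost and blinding.** The resting NRS averages three ratings, and walking pain is a fourth. Taking them during supervised exercise in one arm and by telephone in the other would make ascertainment differ by arm. This stands and shapes the fix.

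**Conclusion.** The point holds in limited form. The schedule and the exclusions together reduce the planned model to a complete-case comparison of change in NRS pain, so the advantages the article cites do not reach the primary outcome. About 10 of 40 participants would have no post-baseline pain score.

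A bias of about 0.2 points towards HBRX is a reasonable indication. It rests on assumed SD 2, correlation 0.5–0.7 and pain-driven loss in HBRX only. It applies to a baseline-adjusted comparison with equal correlations, or to unadjusted change with decaying correlations. Unadjusted change under equal correlations shows none if the level of pain drives dropout, and 0.33–0.42 if lack of improvement does. The article gives no SD, correlation or reasons for dropout, so neither size nor direction can be fixed from it. It does not support a reading that the trial's result will be invalid.

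**What to change.** 1. Collect the resting NRS (current, worst and best over 24 h) and the walking-pain rating with the week 4 and week 8 medication self-reports. Use the same self-report mode in both arms, and do not collect them through the exercise supervisor.
2. Replace the exclusion of dropouts, participants with missing data and non-compliers with inclusion of every randomised participant who has any NRS rating.
3. Fit the mixed model to baseline and weeks 4, 8 and 12 with a group-by-time term. Keep the week-12 contrast as the primary estimate.

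The cost is four short ratings at two existing reports, an amendment, and a rewritten final part of Statistical analysis with the matching sentence in Compliance and attrition. Recruitment was incomplete at submission, so later participants could still benefit. Those already past week 8 will lack the ratings, and anyone leaving before week 4 gains no post-baseline value.
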